### **8.7 Premature termination of the study**

Alitretinoin is registered for the treatment of hand eczema. Azathioprine has been used for decades to treat hand eczema and atopic dermatitis, among other dermatoses. Therefore we do not expect a substantial number of unexpected serious adverse events.

If an unforeseen substantial amount of (unexpected) serious adverse events occur, we will consider premature termination of the study.

## 9. SAFETY REPORTING

### 9.1 Section 10 WMO event

In accordance to section 10, subsection 1, of the WMO, the investigator will inform the subjects and the reviewing accredited METC if anything occurs, on the basis of which it appears that the disadvantages of participation may be significantly greater than was foreseen in the research proposal. The study will be suspended pending further review by the accredited METC, except insofar as suspension would jeopardise the subjects' health. The investigator will keep all subjects informed.

### 9.2 AEs, SAEs and SUSARs

#### 9.2.1 Adverse events (AEs)

Adverse events are defined as any undesirable experience occurring to a subject during the study, whether or not considered related to the investigational product. All adverse events reported spontaneously by the subject or observed by the investigator or his staff will be recorded.

#### 9.2.2 Serious adverse events (SAEs)

A serious adverse event is any untoward medical occurrence or effect at any dose that:

- results in death;
- is life threatening (at the time of the event);
- requires hospitalisation or prolongation of existing inpatients' hospitalisation;
- results in persistent or significant disability or incapacity;
- is a congenital anomaly or birth defect;

Any other important medical event that may not result in death, be life threatening, or require hospitalization, may be considered a serious adverse experience when, based upon appropriate medical judgement, the event may jeopardize the subject or may require an intervention to prevent one of the outcomes listed above.

The investigator will report the SAEs through the web portal *ToetsingOnline* to the accredited METC that approved the protocol, within 15 days after the investigator has first knowledge of the serious adverse events.

SAEs that result in death or are life threatening should be reported expedited. The expedited reporting will occur not later than 7 days after the responsible investigator has first knowledge of the adverse event. This is for a preliminary report with another 8 days for completion of the report.

### **9.2.3 Suspected unexpected serious adverse reactions (SUSARs)**

Adverse reactions are all untoward and unintended responses to an investigational product related to any dose administered.

Unexpected adverse reactions are SUSARs if the following three conditions are met:

1. the event must be serious (see chapter 9.2.2);
2. there must be a certain degree of probability that the event is a harmful and an undesirable reaction to the medicinal product under investigation, regardless of the administered dose;
3. the adverse reaction must be unexpected, that is to say, the nature and severity of the adverse reaction are not in agreement with the product information as recorded in:
  - Summary of Product Characteristics (SPC) for an authorised medicinal product;
  - Investigator's Brochure for an unauthorised medicinal product.

The investigator will report expedited the following SUSARs through the web portal *ToetsingOnline* to the METC:

- SUSARs that have arisen in the clinical trial that was assessed by the METC;
- SUSARs that have arisen in other clinical trials of the same investigator and with the same medicinal product, and that could have consequences for the safety of the subjects involved in the clinical trial that was assessed by the METC.

The remaining SUSARs are recorded in an overview list (line-listing) that will be submitted once every half year to the METC. This line-listing provides an overview of all SUSARs from the study medicine, accompanied by a brief report highlighting the main points of concern.

The expedited reporting of SUSARs through the web portal *ToetsingOnline* is sufficient as notification to the competent authority.

The investigator will report expedited all SUSARs to the competent authorities in other Member States, according to the requirements of the Member States.

The expedited reporting will occur not later than 15 days after the investigator has first knowledge of the adverse reactions. For fatal or life threatening cases the term will be maximal 7 days for a preliminary report with another 8 days for completion of the report.

Since the treating physician is not blinded, there is no need to break the code in case of an SUSAR.

### **9.3 Annual safety report**

In addition to the expedited reporting of SUSARs, the investigator will submit, once a year throughout the clinical trial, a safety report to the accredited METC, competent authority, and competent authorities of the concerned Member States.

This safety report consists of:

- a list of all suspected (unexpected or expected) serious adverse reactions, along with an aggregated summary table of all reported serious adverse reactions, ordered by organ system, per study;
- a report concerning the safety of the subjects, consisting of a complete safety analysis and an evaluation of the balance between the efficacy and the harmfulness of the medicine under investigation.

### **9.4 Follow-up of adverse events**

All AEs will be followed until they have abated, or until a stable situation has been reached. Depending on the event, follow up may require additional tests or medical procedures as indicated, and/or referral to the general physician or a medical specialist. SAEs need to be reported till end of study within the Netherlands, as defined in the protocol.

### **9.5 Data Safety Monitoring Board (DSMB)**

No DSMB is established, since this is a daily practice study. In case of life-threatening diseases usually the implementation of a DSMB is indicated from an ethical point of view. But hand eczema is a non-critical indication. Frequent laboratory assessments will reduce the possibility of serious adverse events to a minimum. The patient population in this clinical trial exists of legal competent adults and the study drugs alitretinoin and azathioprine are well-investigated, well-characterized drugs.

## 10. STATISTICAL ANALYSIS

This trial is designed to demonstrate a superior response to azathioprine compared to alitretinoin in the treatment of severe chronic non-hyperkeratotic hand eczema. Response to treatment is defined as an improvement of  $\geq 2$  steps on the Physician Global Assessment (PGA) developed by Ruzicka et al (8,9) at 24 weeks of treatment.

All analysis will be based on the intention-to-treat principle to guard against attrition bias. Subjects might not only withdraw because the study drug works insufficient, they might also withdraw when their hand eczema is cured.

Missing values will be handled in a way that is dependent on assumptions about the missing data. If the extent and pattern of missing data is known (e.g. missing at random (MAR), missing completely at random (MCAR), missing not at random (MNAR)), an analysis will be chosen that is valid under a plausible assumption about the missing data (probably mixed models). This is according to a strategy proposed by White et al. (28)

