#### **4.4 Sample size calculation**

This trial hypothesizes a superior response to azathioprine compared to alitretinoin in the treatment of severe chronic non-hyperkeratotic hand eczema.

A sample size of 52 in each group will have 80% power to be able to reject the null hypothesis of no difference between alitretinoin and azathioprine, using a chi-square test with a two-sided 0.05 significance level. In this calculation we used the following assumptions: randomization ratio is 1:1, and we expected the percentage of responders in the alitretinoin group to be 33% (10). Literature on the efficacy of azathioprine on hand eczema in terms of PGA is lacking. From a retrospective assessment of available patient data from our department, combined with clinical experience, we estimate 60% responders in the azathioprine group. We anticipate a drop-out of maximal 10% of randomized patients; a small percentage prior to first application of study drugs due to excluding laboratory measurements and a larger percentage during follow up, mainly due to subjective side effects. We therefore plan to include 116 patients in total, 58 in the alitretinoin group and 58 in the azathioprine group. (Calculated with the sample size

calculator of the Department of Biostatistics, Vanderbilt University, United States,  
available at <http://biostat.mc.vanderbilt.edu/wiki/Main/PowerSampleSize>.)

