### 6.5 Description and justification of route of administration and dosage

Group I will receive an oral *alitretinoin* capsule of 30mg once daily for a total of 24 weeks. In a dose-finding study, the effectiveness and tolerability of this dose was established and it is recommended to use this as the standard dose for the prescription of alitretinoin in hand eczema. (8,10)

Group II will receive oral *azathioprine* tablets twice daily in a dose of 1.5 or 2.5mg/kg/day, depending on the thiopurine methyltransferase (TPMT) activity. A blood sample to measure TPMT activity will be obtained at the randomization visit. In thiopurine metabolism, the activity of the gene that encodes for the expression of the TPMT enzyme has an important effect on the toxicity of thiopurines in the human body. Genetic interpersonal differences lead to a difference in TPMT activity. Patients with low or absent activity of TPMT (0.3% of patients) have a risk of fatal myelosuppression when given normal doses of thiopurines. The result of the test is available in 3-4 weeks in our center. Patients will be allowed to continue their current topical treatment (if this is in accordance with the in-/exclusion criteria) for three more weeks and are required to taper the strength of topical corticosteroids to maximum class 2 during the week prior to baseline. At the azathioprine baseline visit (4 weeks following randomization visit) patients receive a dosage of azathioprine tailored to their TPMT activity. Patient with a low or absent TPMT activity (indicating homozygous or compound heterozygous mutations) will be excluded from the study. Patients with intermediate activity of TPMT (indicating heterozygous mutation) will receive 1.5mg/kg/day. Dosage in patients with normal to high activity levels of TPMT (indicating homozygous wild-type) will receive 2.5mg/kg/day. This is in accordance with current guidelines. (20)

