## 8. METHODS

### 8.1 Study parameters/endpoints

#### 8.1.1 Main study parameter/endpoint

##### *Severity of hand eczema*

The Physician Global Assessment (PGA) developed by Ruzicka et al, covers 5 degrees of severity (clear, almost clear, mild, moderate, severe) and takes into account the intensity and percentage of hand surface involved. (8,9) Response to treatment is defined as an improvement of  $\geq 2$  steps on the PGA. Severe hand eczema is defined as responding to treatment if a status of at least 'mild' is achieved. Moderate hand eczema is defined as responding to treatment if a status of at least 'almost clear' is achieved.

In this study the main endpoint is the between-group difference in response to treatment between baseline and 24 weeks of treatment.

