### **8.6 Follow-up of subjects withdrawn from treatment**

Subjects withdrawn from treatment will continue to be treated at our center, outside the study. All efforts will be made to report the observations for the reason(s) for premature withdrawal and the time of occurrence. If an adverse event is the reason for withdrawal, the physicians of our department will administer therapy as clinically indicated. All serious adverse events and those adverse events for which the relationship to the study drug is plausibly related will be followed up until they have returned to baseline status or stabilized.

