##### e. Analysis of potential effect

*Alitretinoin (from SPC text) (10)*

The recommended dose range for alitretinoin is 10 mg - 30 mg once daily.

The recommended start dose for alitretinoin is 30 mg once daily. A dose reduction to 10 mg once daily may be considered in patients with unacceptable adverse reactions to the higher dose. In studies investigating 10 mg and 30 mg daily doses, both doses resulted in clearing of the disease. The 30 mg dose provided a more rapid response and a higher response rate. The 10 mg daily dose was associated with fewer adverse events.

A treatment course of alitretinoin may be given for 12 to 24 weeks depending on response. Discontinuation of therapy should be considered for patients who still have severe disease after the initial 12 weeks of treatment. In the event of relapse, patients may benefit from further treatment courses of alitretinoin.

The capsules should be taken with a meal once daily.

Alitretinoin should not be prescribed if the patient's eczema can be adequately controlled by standard measures, including skin protection, avoidance of allergens and irritants, and treatment with potent topical corticosteroids.

Risks of alitretinoin treatment are described in paragraph 6.4.

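### The primary outcome is not collected after withdrawal, although the protocol foresees withdrawal that depends on response in both directions

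*Protocol*

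**What the plan says.** Protocol Section 8.1.1 defines response as an improvement of at least 2 PGA steps and states that "the main endpoint is the between-group difference in response to treatment between baseline and 24 weeks of treatment". Section 10.1 compares the two proportions by chi-square test, or Fisher's exact test if appropriate.

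Section 10 puts all analyses on an intention-to-treat footing to protect against bias from attrition, and explains why: "Subjects might not only withdraw because the study drug works insufficient, they might also withdraw when their hand eczema is cured". For missing values it says only that a method valid under a plausible assumption will be chosen, with mixed models named as the probable one.

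On follow-up, Section 8.6 says: "Subjects withdrawn from treatment will continue to be treated at our center, outside the study". It provides for recording the reason for and time of withdrawal, and for following certain adverse events. It asks for no further PGA. Section 8.4 lets patients leave at any time for any reason. Section 8.4.1 lists criteria for withdrawal, including no PGA improvement at week 12; cure is not on that list.

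Tables 1 and 2 in Section 8.3 schedule PGA at baseline and at weeks 4, 8, 12 and 24.

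**The concern.** Intention-to-treat analysis protects against attrition bias only if outcomes are collected on the patients who stop, or if their absence can be modelled credibly. Here the protocol names success and failure as reasons for leaving, and its follow-up rule collects the primary outcome in neither case. Missingness is then related to the outcome in both directions, so no single default suits everyone: counting leavers as non-responders is reasonable for patients withdrawn for lack of effect and doubtful for patients who left clear.

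Two features make it harder to repair afterwards. No scheduled visit falls between weeks 12 and 24. For a patient who leaves in that interval, the last scheduled PGA is the week-12 one, which may predate the cure and cannot show a relapse. Also, the chi-square test needs a yes or no for each patient, and the tentative reference to mixed models does not say how that value is obtained.

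At stake is the primary comparison: its result could depend on a scoring rule that the protocol leaves open.

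**Working it through.** **Inputs.** Section 4.4 gives responder rates of 33% (alitretinoin) and 60% (azathioprine), "randomization ratio is 1:1", "using a chi-square test with a two-sided 0.05 significance level", a drop-out of at most 10%, and 58 patients per arm. It gives no rate of withdrawal after cure. It attributes drop-out to laboratory exclusions and mainly to subjective side effects.

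**1. The plan's own figure.** Section 4.4 states: "A sample size of 52 in each group will have 80% power". With the pooled-variance formula without continuity correction,

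n = [1.96·√(2·p̄(1−p̄)) + 0.842·√(p₁(1−p₁) + p₂(1−p₂))]² / (p₁−p₂)², with p̄ = 0.465,

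the result is 52.4, or 53 rounded up. Power is 79.7% at 52 per arm and 83.9% at 58. Inflating 52 by 1/(1−0.10) gives 57.8, so 58 per arm and 116 in total. The stated sample size reproduces; there is no arithmetic error.

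**2. Sensitivity of the test result to the scoring rule.** Expected responders are 0.33×58 ≈ 19 and 0.60×58 ≈ 35. The allowance, if spread evenly over the arms, is 0.10×58 ≈ 6 per arm. The uncorrected statistic is χ² = N(ad−bc)² / (product of the four margins). Suppose that some azathioprine successes have no week-24 PGA and that no alitretinoin success is lost:

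| Handling | Alitretinoin | Azathioprine | χ² | p |
|---|---|---|---|---|
| All outcomes observed | 19/58 | 35/58 | 116×928²/(58·58·54·62) = 8.87 | 0.003 |
| Five scored as failures | 19/58 | 30/58 | 116×638²/(58·58·49·67) = 4.28 | 0.039 |
| Six scored as failures | 19/58 | 29/58 | 116×580²/(58·58·48·68) = 3.55 | 0.059 |
| Six dropped | 19/58 | 29/52 | 110×694²/(58·52·48·62) = 5.90 | 0.015 |

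Six is an upper bound: every drop-out in that arm would have to be a cured responder.

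**3. Sensitivity of difference and power.** Assume a share c of true responders leaves cured with no week-24 PGA, 58 per arm and no other loss. The observed rate is p(1−c) if leavers count as failures, p(1−c)/(1−pc) if they are dropped, and p if they count as responders. The difference is azathioprine minus alitretinoin.

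| Share leaving | Rule | Difference (points) | Power |
|---|---|---|---|
| None | – | 27.0 | 83.9% |
| 10% in both arms | failures | 24.3 | 76.3% |
| 10% in both arms | dropped | 26.7 | 81.7% |
| 10% in both arms | responders | 27.0 | 83.9% |
| 10%, azathioprine only | failures | 21.0 | 62.9% |
| 10%, azathioprine only | dropped | 24.4 | 74.7% |
| 10%, alitretinoin only | failures | 30.3 | 91.7% |

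The shift can go either way, depending on the rule and on which arm loses more successes.

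**The case against.** The strongest defence is that the protocol has seen the problem. It says only that cured patients might leave, answers with intention-to-treat, and follows with a missing-data strategy that names data missing not at random. PGAs at weeks 4, 8 and 12 exist for most leavers. Patients stay at the same clinic, where scoring the PGA is routine. Detailed imputation rules commonly sit in a statistical analysis plan, and that document is not shown.

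Much of this stands: the absence of an imputation rule is not itself the point. What remains is data collection. An analysis plan can choose a rule for missing scores, but it cannot supply a blinded week-24 PGA that nobody was asked to obtain, and routine care outside the study guarantees neither the timing nor the blinding.

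Three stronger readings are tempting, and the document supports none of them.

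- A reader might infer that cured leavers cannot be scored and drop out of the responder count. No section excludes them or scores them as failures; the protocol simply gives them no responder status.
- A reader might see a contradiction on course length between Section 6.5, "capsule of 30mg once daily for a total of 24 weeks", and Section 13.1e, "A treatment course of alitretinoin may be given for 12 to 24 weeks depending on response". The latter is product text quoted as such, and a labelled range that includes 24 weeks does not conflict with a 24-week trial course.
- A reader might infer that the bias favours azathioprine, because its onset is slow and early cures would be commoner with alitretinoin. That is conjecture: the protocol has no data on it, and the last table shows movement in both directions.

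**Conclusion.** The point holds as a gap between the stated aim of the analysis and the follow-up rule. The primary outcome is not collected after withdrawal, while the protocol foresees or requires withdrawals that depend on response: after cure, for insufficient effect, and at week 12 for no PGA improvement.

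The size and direction of any bias are unknown. The range from p=0.003 to p=0.059 (or p=0.015 if the six are dropped) shows that the primary conclusion can turn on the scoring rule within the protocol's own drop-out allowance. It is an extreme case: six azathioprine successes lost, no alitretinoin success lost, and a scoring rule that the protocol does not state. With five scored as failures the result stays below 0.05. The power figures likewise rest on assumed leaver shares. The change is worth making because it is cheap and must be in place before patients leave.

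**What to change.** In Sections 8.6 and 10, separate stopping study drug from leaving the study. State that patients who stop study drug for any reason (cure, lack of efficacy, adverse event), unless they withdraw consent, are asked to attend the week-24 visit for the blinded PGA, and that this score counts as observed in the primary analysis.

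Where that PGA is still missing, keep the patient in the denominator and report the primary result twice: once with the last observed response status and once as non-response.

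The cost is protocol wording and one severity score in patients who already attend the same centre. The downsides are that some patients will not return, and that part of the week-24 outcome will be measured off study drug or on other treatment. The report should say how many scores were obtained that way in each arm.

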### 10.1 Primary study parameter

#### *Severity of hand eczema*

Between-group difference in response to treatment between baseline and 24 weeks of treatment. For comparison of proportions in the alitretinoin and azathioprine group the chi-square test, or Fisher's exact test if appropriate, will be used.

### 10.2 Secondary study parameters

#### *Severity of hand eczema*

- Between-group difference in mean change in PGA between baseline and 12 and 24 weeks. For comparison of mean change between the alitretinoin and azathioprine group at week 12 and 24, the Student's t-test or Mann-Whitney U-test will be used, depending on distribution of data.
- Between-group difference in response to treatment between baseline and 12 weeks of treatment. For comparison of proportions in the alitretinoin and azathioprine group the chi-square test will be used.
- Between-group difference in mean change between baseline and week 4, 8, 12 and 24, assessed by the Hand Eczema Severity Index (HECSI) score. This will be described graphically. For comparison of mean change between the

alitretinoin and azathioprine group at week 12 and 24, the Student's t-test or Mann-Whitney U-test will be used, depending on distribution of data.

- Between-group difference in time to response (time to first PGA improvement of  $\geq 2$  steps). This will be analysed using a Kaplan-Meier product limit estimator. For comparison between the alitretinoin and azathioprine group the Log-rank test will be used.

*Patient rated outcome measures (PROMs):*

*Quality of life*

- Between-group mean change in quality of life between baseline and 12 and 24 weeks, assessed by the Quality Of Life in Hand Eczema Questionnaire (QOLHEQ). Clinically relevant improvement is defined as an absolute improvement of 15 points (theoretically corresponding to an improvement of  $\geq 1$  point on 50% of the questions) compared to baseline. For comparison of proportions of patients rated as having clinically relevant improvement in the alitretinoin and azathioprine group, the chi-square test will be used.

*Patient reported improvement*

- Between-group difference in patients reporting improvement as 'clear or almost clear' at week 12 and 24, assessed by Patient Global Assessment (PaGA). For comparison of proportions of patients rated as 'clear or almost clear' in the alitretinoin and azathioprine group, the chi-square test will be used.

*Safety and tolerability*

- Adverse events in both groups will be registered.

*Cost-utility and cost-effectiveness*

- For each group (alitretinoin and cyclosporine), the mean EQ-5D scores overall and of each dimension will be reported. Results from the descriptive system of the EQ-5D-5L will be converted to a utility index value, a population based (social) value specific for the Netherlands. With this value, Dutch utility values will be calculated in order to determine the quality adjusted life years (QALYs) over the study period. Mean values of the EQ-VAS will be reported with a 95% confidence interval. For comparison of means, the Student's t-test or Mann-Whitney U-test will be used, depending on distribution of data.
- The incremental cost-effectiveness ratio (ICER) will be calculated and reported as €/QALY. Effect will be assessed with the PGA. Costs will be assessed as described in paragraph 8.2.

- A regression model will be used to estimate the association between QALYs and the PGA.

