### 8.1.3 Other study parameters

At baseline age, sex, Body-Mass-Index, current and history of atopic dermatitis (both defined by U.K. Working Party criteria) (23), age of onset of atopic dermatitis, age of onset of hand eczema, current use of statins, current use of thyromimetics, currently smoking and amount of pack-years will be registered because these might be confounders. (2,24) Pack years are calculated by multiplying the total years smoked with the average packs per day smoked over these years. (25) For this, we use the online Smoking Pack Years Calculator, created by dr NJ Masters and C Tutt. (26)

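### HECSI change and EQ-5D/QALY means are compared without adjusting for the baseline scores the trial collects, which costs precision and leaves conditional bias on these secondary outcomes

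*Protocol*

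**What the plan says.** Protocol section 10.2 names the between-group tests.

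- **HECSI change, weeks 12 and 24:** "For comparison of mean change between the alitretinoin and azathioprine group at week 12 and 24, the Student's t-test or Mann-Whitney U-test will be used". The shape of the observed data decides between the two. Section 10.3 gives the procedure: visual inspection, a Q-Q plot, a normality test if in doubt, and Welch's test for unequal variances.
- **EQ-5D scores and QALYs:** "For comparison of means, the Student's t-test or Mann-Whitney U-test will be used, depending on distribution of data".

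Tables 1 and 2 in section 8.3 schedule HECSI and EQ-5D at the start of treatment in both arms, so baseline values exist for every treated patient. Section 8.1.3 lists further baseline characteristics that "will be registered because these might be confounders".

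The Protocol names no between-group analysis that adjusts for a baseline score. Section 10 mentions mixed models only as a likely way to deal with missing data. The one regression in section 10.2 relates QALYs to the PGA, not treatment to outcome.

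**The concern.** HECSI change subtracts the baseline with a fixed weight of 1, whatever its relation to follow-up. EQ-5D means give it no weight at all. Neither is the efficient choice when the baseline predicts the follow-up score. Both also leave an error in the estimate when the arms differ at baseline by chance, which is not negligible with about 52 patients per arm.

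The test is chosen after the distribution has been inspected. Mann-Whitney does not estimate the difference in mean change that the HECSI endpoint names, so the reported quantity may change with the data.

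At stake are wider intervals than necessary for HECSI and the cost-utility outcomes, and estimates that shift with chance imbalance.

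**Working it through.** **Plan's own figure.** Section 4.4 says "A sample size of 52 in each group will have 80% power", with 33% and 60% responders, "randomization ratio is 1:1", "using a chi-square test with a two-sided 0.05 significance level". The pooled formula without continuity correction is

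n = [1.960·√(2 × 0.465 × 0.535) + 0.842·√(0.33 × 0.67 + 0.60 × 0.40)]² / 0.27² ≈ 52.4, i.e. 53 per arm.

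Power at 52 per arm is 79.7%, and 104/0.90 = 115.6 gives 116 in total. The stated figures reproduce. They concern the primary endpoint only; the Protocol has no power calculation for HECSI or EQ-5D.

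**Assumed inputs.** r from 0.3 to 0.7, with equal SDs (s) at baseline and follow-up. Neither is in the Protocol.

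**HECSI precision.**
- Var(change) = 2s²(1 − r)
- Var(ANCOVA) = s²(1 − r²)
- Ratio = (1 + r)/2

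The last column is Φ(2.802/√ratio − 1.960), for an effect that the change-score test detects with 80% power.

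| r | Variance ratio | SE reduction | Patients per arm matching 52 | ANCOVA power |
|---|---|---|---|---|
| 0.3 | 0.65 | 19% | 33.8 | 93.5% |
| 0.5 | 0.75 | 13% | 39.0 | 89.9% |
| 0.7 | 0.85 | 8% | 44.2 | 86.0% |

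**Unequal SDs.** With k = baseline SD / follow-up SD, the ratio is (1 − r²)/(1 + k² − 2rk). At k = 0.5:
- r = 0.3: 0.91/0.95 = 0.96
- r = 0.5: 0.75/0.75 = 1.00
- r = 0.6: 0.64/0.65 = 0.98

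So the gain is only 0 to 4% in that case.

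**Chance imbalance.** With 52 per arm, the baseline difference has SE √(2/52) = 0.196 SD, so its 95% range is ±1.96 × 0.196 = ±0.38 SD. For an imbalance d, equal SDs:
- The expected follow-up difference with no treatment effect is r·d.
- The change score is therefore off by r·d − d = −(1 − r)·d. At d = 0.38 SD this is 0.27 SD for r = 0.3 and 0.11 SD for r = 0.7, in the direction opposite to the imbalance.
- An unadjusted follow-up mean, as for EQ-5D, is off by r·d: 0.11 SD for r = 0.3 and 0.27 SD for r = 0.7.
- For a follow-up mean, ANCOVA variance is (1 − r²) of the unadjusted variance: 0.91, 0.75 and 0.51 for r = 0.3, 0.5 and 0.7.

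**Primary endpoint, for comparison.** In 2,000 simulated trials per setting (52 per arm, 33% v 60%), chi-square was compared with logistic regression adjusted for one baseline covariate.

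| Covariate log-odds per SD | Chi-square power | Adjusted power |
|---|---|---|
| 0 | 83.1% | 81.1% |
| 0.3 | 82.1% | 80.9% |
| 0.5 | 83.4% | 83.0% |
| 0.8 | 82.1% | 84.8% |
| 1.2 | 83.1% | 88.7% |

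Simulated type I error was about 5 to 6% for both tests.

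**The case against.** **The gain rests on assumed figures.** This stands. The 15 to 35% variance reduction needs equal SDs and an assumed r, and it nearly vanishes at k = 0.5. The 0–360 HECSI range does not show that baseline scores vary widely in a population selected for severity. However, in large samples ANCOVA is never less precise than the change score: the difference in variance is (s_x − r·s_y)², with s_x and s_y the baseline and follow-up SDs, and this cannot be negative.

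**The azathioprine baseline is not pre-randomisation.** This also stands. By section 6.5 and Table 2, that arm is scored at V0a, four weeks after open-label randomisation. Topical treatment continues in between and is tapered in the last week. The alitretinoin arm is scored at the randomisation visit. A baseline difference therefore need not be chance, and ANCOVA would adjust for a post-randomisation value in one arm. This does not favour the planned method: the change score subtracts the same value with full weight, whereas ANCOVA weights it by its slope.

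**An analysis plan may add adjusted models.** It may, and the unused covariates of section 8.1.3 are not a finding for that reason. But the Protocol itself names the unadjusted tests for these outcomes.

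**The choice of test has a procedure.** Section 10.3 does set one. It still depends on the observed data and can lead to a test that does not estimate the named mean difference.

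**The primary analysis.** A reader might infer that the primary chi-square is deficient too. The Protocol does not support that. The test is valid and matches the sample-size basis, and response is already defined relative to the baseline grade. Entry requires severe disease on the PGA (section 4.2), so baseline PGA is close to constant and adjusting for it gains almost nothing. Another covariate would have to be strongly prognostic to matter. The near-constant baseline likewise means little gain for PGA change.

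**QOLHEQ.** A reader might count it among the raw change scores. Section 10.2 tests it as the proportion improving by 15 points, using chi-square.

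**Conclusion.** The point holds for HECSI change and for EQ-5D/QALY means. Under equal SDs and r of 0.3 to 0.7, the planned HECSI comparison has 1/0.85 = 1.18 to 1/0.65 = 1.54 times the variance of ANCOVA. A baseline imbalance at the edge of its 95% range would move the estimate by about 0.11 to 0.27 SD. With baseline SD half of follow-up SD, the precision gain is only 0 to 4% for r of 0.3 to 0.6.

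A reader might conclude that chance imbalance goes uncorrected throughout. That is true of the EQ-5D means; change scores over-correct it when SDs are equal. Nor are the planned tests invalid: averaged over randomisations, type I error is preserved. This is a matter of efficiency and conditional bias on secondary outcomes, and it does not touch the primary analysis or the planned 116 patients.

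**What to change.** In section 10.2:

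- **HECSI change:** prespecify ANCOVA at weeks 12 and 24, or one repeated-measures model over weeks 4, 8, 12 and 24, with baseline HECSI as covariate. The repeated-measures model fits the mixed models that section 10 already expects for missing data. It also keeps the earlier scores of patients withdrawn at week 12 under section 8.4.1.
- **EQ-5D and QALYs:** adjust for baseline utility.
- **Reporting:** give the adjusted difference with its 95% CI, and keep Mann-Whitney as a sensitivity analysis only.
- **Caveat:** state that the azathioprine baseline is measured four weeks after randomisation, so the adjusted comparison, like the planned change score, conditions on a post-randomisation value in that arm.
- **Primary:** leave the chi-square unchanged.

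The cost is wording only, settled before outcome data are seen: no extra patients, and the scores used are already scheduled. Removing the caveat altogether would need HECSI and EQ-5D at the azathioprine randomisation visit, which Table 2 does not schedule. That is a separate decision and not a condition for this change.
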